##### Aim 2: To Assess the Therapeutic Effect of CBT-I in Individuals With a Subacute Concussion on the Severity and Number of Postconcussion Symptoms, Anxiety, and Depression

An independent samples *t* test will be used to determine if there is a significant difference in percent change for the PCSS, BAI, and BDI between the CBT-I condition and the WLC group. To assess maintenance, paired samples *t* tests will be used to determine if there is a significant difference from the following time points: from the reassessment following CBT-I (reassessment 1 for the CBT-I group; reassessment 2 for the WLC group) to the immediate reassessment following the typical activities period (reassessment 2 for the CBT-I Initial group; reassessment 3 for the WLC group), or from reassessment following CBT-I to delayed reassessment (reassessment 1 to reassessment 3 for the CBT-I group). The percentage of participants who meet the MCID criteria for each outcome will be reported (12 points for the PCSS, 4 points for the total number of symptoms on the PCSS, 4 points on the BAI, and 5 Points on the BDI [40,45,46]). In the event that the data do not meet the assumptions for parametric *t* tests, nonparametric tests (Mann-Whitney *U* test for independent samples and Wilcoxon signed rank test for paired samples) will be used.

##### Aim 3: To Evaluate the Relationship Between Improvement in Sleep Outcomes and Postconcussion Symptoms

Two simple linear regressions will be run to evaluate the relationship between improvement in sleep outcomes and postconcussion symptoms. The first simple linear regression will determine if change in ISI from preintervention to postintervention stages (predictor variable) will predict changes in postconcussion severity (dependent variable). The second simple linear regression will determine if change in the ISI from preintervention to postintervention stages (predictor variable) will predict changes in the number of postconcussion symptoms (dependent variable). If there are significant differences at baseline in age, gender, medication use, number of concussions, and receiving other services between the two groups, the variables will be entered into the model as a covariate, and the 2 models will be rerun.

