## Introduction

### Background

Between 1.7 and 3.8 million people in the United States experience a concussion each year, and the prevalence of concussions continues to increase [1-3]. A concussion injury results from a rotational or linear force to the head, neck, or face, causing injury to the brain [2,4]. Injuries from a concussion result in a number of symptoms termed *postconcussion symptoms* [5], which can be categorized into 4 different domains: somatic, cognitive functioning, mood regularity, and sleep dysregulation [5].

Sleep dysregulation is a risk factor for prolonged recovery. One recent systematic review found that poor sleep was predictive of poor long-term outcomes in the acute phase of concussion recovery [6], while another systematic review found that poor sleep in the chronic phase of recovery was associated with poor cognitive functioning (executive function and working memory) and emotional regulation [7]. Currently, it is unknown if treatment for sleep disturbances in individuals with a concussion could impact recovery.

The causes of sleep disturbances are multifactorial. Axonal damage that occurs during the concussion injury can result in dysregulation of the sleep and arousal centers in the brain [6,8-11]. Furthermore, medication use, new onset or increase in anxiety or depression, or a change in routine and the sleep schedule can contribute to sleep disturbances [6,12,13]. Sleep complaints can be present immediately following a concussion or within the first few days or weeks following the injury. The most reported sleep disturbance in individuals with a concussion, insomnia, is experienced by nearly 50% of those individuals [14]. Chronic insomnia is defined as difficulty in falling asleep or staying asleep 3 or more days a week for more than 3 months [15,16].

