#### Postconcussion Symptom Severity Questionnaires

Postconcussion symptom severity and the number of symptoms will be assessed using the Post-Concussion Symptom Scale (PCSS) [43]. The severity of 22 concussion-related symptoms is assessed on a Likert scale ranging 0-6 with 0=“no symptom” and 6=“extreme symptom” [44]. A score of 132 is the maximum, indicating that all symptoms are severe [44]. The number of postconcussion symptoms will be assessed by counting the number of symptoms that the participant identified as having a severity of 1 or higher on the PCSS. A score of a 1 indicates that the symptom is mild but still noticeable.

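### Aim 3 regresses change in the full PCSS on change in ISI, although the protocol counts sleep dysregulation among postconcussion symptoms, so part of any positive association is built in

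*Protocol article*

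**What the plan says.** The Background describes postconcussion symptoms as a group "which can be categorized into 4 different domains: somatic, cognitive functioning, mood regularity, and sleep dysregulation".

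The section on postconcussion symptom questionnaires measures those symptoms with the PCSS: "The severity of 22 concussion-related symptoms is assessed on a Likert scale ranging 0-6". It adds: "A score of 132 is the maximum, indicating that all symptoms are severe". The number of symptoms is obtained by "counting the number of symptoms that the participant identified as having a severity of 1 or higher on the PCSS". No item is set aside for either score.

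The statistical approach to Aim 3 plans two simple linear regressions. The predictor in both is "change in ISI from preintervention to postintervention stages (predictor variable". In the first model this "will predict changes in postconcussion severity (dependent variable"; in the second it "will predict changes in the number of postconcussion symptoms (dependent variable". The only adjustment foreseen is for baseline characteristics that differ between the two groups.

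The Abstract calls the postconcussion symptoms concomitant to the sleep problem. Expected Findings and Conclusions read the planned association as evidence that resolving insomnia goes with, and may bring about, improvement in postconcussion symptoms.

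**The concern.** The ISI measures insomnia severity. On the protocol's own definition, the PCSS covers a symptom set that includes disturbed sleep. Sleep complaints then enter both sides of each regression. A participant who sleeps better and is otherwise unchanged has a lower ISI and, through the sleep items, a lower PCSS total. Across participants this gives a positive slope, in the direction hypothesised for Aim 3, without any change in headache, concentration or mood.

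The interpretation of Aim 3 depends on this. The clinically interesting statement is that treating insomnia goes with recovery in the other symptoms. A positive slope on the full score cannot separate that from one insomnia measure tracking another. The baseline covariates do not help, because the overlap lies in the outcome and not in group imbalance.

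**Working it through.** **1. Are all items kept?** 22 items × 6 points = 132, which reproduces the stated maximum. The severity score therefore drops nothing, and the count takes every item scored 1 or higher.

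**2. Is the overlap separated anywhere?** The Aim 3 section names the outcomes as postconcussion severity and number of symptoms. It plans no sleep-excluded score, and neither do the sections on the PCSS or on Aim 2.

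**3. How large could the built-in part be?** The documents do not list the PCSS items, so this step is an illustration. Assumptions:

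- m of the 22 items concern sleep, m = 1 to 5;
- all item changes have equal variance, set to 1;
- each sleep item's change correlates ρ = 0.5 to 0.6 with ISI change;
- non-sleep items are unrelated to ISI change (no true association outside sleep);
- sleep items correlate 0.4 with each other, and non-sleep items c = 0.1 to 0.3 with each other;
- sleep and non-sleep items are uncorrelated;
- n = 40, the number enrolled.

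The built-in correlation between ISI change and PCSS severity change is

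r = mρ / √V, with V = [m + m(m−1)·0.4] + [(22−m) + (22−m)(21−m)·c].

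The chance of two-sided p < .05 follows from Fisher's z: Φ(z − 1.96) + Φ(−z − 1.96), with z = arctanh(r)·√37.

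Lowest case, m = 1, ρ = 0.5, c = 0.3: V = 1 + (21 + 21·20·0.3) = 148, so r = 0.5/12.17 = 0.04. Then z = 0.25 and the chance is 0.044 + 0.014 = 6%.

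Highest case, m = 5, ρ = 0.6, c = 0.1: V = (5 + 20·0.4) + (17 + 17·16·0.1) = 13 + 44.2 = 57.2, so r = 3.0/7.56 = 0.40. Then z = 2.55 and the chance is 72%.

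| Sleep items assumed | Built-in r | Chance of p < .05, n = 40 |
|---|---|---|
| 1 | 0.04–0.08 | 6–7% |
| 2 | 0.09–0.15 | 8–16% |
| 3 | 0.13–0.24 | 13–31% |
| 4 | 0.18–0.32 | 20–51% |
| 5 | 0.24–0.40 | 31–72% |

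The nominal rate is 5%.

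**4. Sensitivity to the cross-correlation.** If sleep and non-sleep items correlate at 0.1, V gains 2·m·(22−m)·0.1. In the highest case this is 2·5·17·0.1 = 17, so V = 74.2, r = 3.0/8.61 = 0.35 and the chance is 60%. For the top 4-item case r falls from 0.32 to 0.28 and the chance from 51% to 43%. The built-in part shrinks but remains.

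**5. The symptom count.** The calculation models a sum of item scores and does not carry over to the count. A sleep item that improves from 5 to 1 takes 4 points off severity and leaves the count unchanged. Only a fall to 0 lowers it. The overlap acts on the count through complete resolution alone, and no figure is offered for it.

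**6. After removal.** With the sleep items taken out of the outcome, the numerator mρ is 0 under the same model and the test returns to 5%. The maximum severity becomes 132 − 6m, that is 126 down to 102 for m = 1 to 5.

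**The case against.** The strongest reply is that the size is unknown. The four-domain statement describes postconcussion symptoms in general and not the PCSS item by item. With a single sleep item the inflation would be close to nothing, and the upper figures rely on sleep and non-sleep items being uncorrelated. This stands. The range shows what could happen and does not estimate what will.

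Second, Aim 3 is the third aim and is worded as an association with postconcussion symptoms as a whole, while the primary outcome is the randomised comparison of ISI. This also stands, and the primary analysis is untouched. It does not rescue the reading given in Expected Findings and Conclusions, which treat insomnia and postconcussion symptoms as two separate things.

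Third, a reader might infer that Aim 2 is biased in the same way. The documents do not support that. Aim 2 compares randomised groups, and a gain on the sleep items is a real effect on the PCSS total. Anxiety and depression are also compared on their own scales, and the stated minimal important differences (12 points and 4 symptoms) are given for the full PCSS.

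Fourth, sensitivity analyses are often left to an analysis plan that is not shown. The point here concerns what the protocol does fix: the scoring and the two dependent variables.

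**Conclusion.** The point holds for Aim 3. On the protocol's own definition, sleep complaints are in both the predictor and the outcomes, so part of any positive association is expected without change in any somatic, cognitive or mood symptom. This is clearest for severity and weaker for the count. The planned regressions alone cannot support a conclusion about concomitant, non-sleep symptoms.

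The existence of the overlap follows from the text; its size does not. Under the assumptions listed, the built-in correlation in the severity model runs from 0.04 to 0.40 and the chance of a significant slope from 6% to 72%, and both are lower if the two item groups are positively correlated.

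A reader might go further and infer that the whole association would be an artefact. Nothing in the documents shows that. A real link between better sleep and the other symptoms may exist, but the analysis as planned cannot isolate it.

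**What to change.** Before analysis, list the PCSS items that belong to the sleep domain. Prespecify the two Aim 3 regressions with severity and symptom count re-scored without those items, and report them beside the full-scale results. Base any claim about non-sleep postconcussion symptoms on the sleep-excluded versions. Fixing the list in advance matters more here because the Randomization section states that the unblinded treating researcher also performs the data analyses.

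Keep the full PCSS as the standard score and as the Aim 2 outcome with its stated minimal important differences. A sleep-excluded PCSS in Aim 2 is optional and descriptive.

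The cost is a re-scoring of item responses that the REDCap questionnaires already collect, two further regressions, and a non-standard subtotal to explain. No new data, visits or participants are needed.

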### Randomization

Following the baseline assessment, participants will be randomized to either the CBT-I initial group (n=20) or the CBT-I WLC group (n=20; Figure 1). A randomization list was developed using SPSS [46]. Participants are not blinded to their group assignment. One researcher (RL) is providing the treatment for this study and is not blinded to group allocation. Questionnaires are sent to participants via REDCap, and participants will be able to answer the questionnaires on their own time and in their own environment. The same researcher (RL) is also performing data analyses for this study.

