#### Statistical Approach

##### Aim 1: To Assess the Therapeutic Effect of CBT-I in Individuals With a Subacute Concussion on Insomnia Symptoms and Sleep Quality

An independent samples *t* test will be used to determine if there is a significant difference in percent change in the ISI (primary outcome) and PSQI between the CBT-I and the WLC conditions. To assess maintenance for each group, paired *t* tests will be used to determine if there is a significant difference at the following time points: from the reassessment following CBT-I (reassessment 1 for the CBT-I group; reassessment 2 for the WLC group) to the immediate reassessment following the typical activities period (reassessment 2 for the CBT-I initial group; reassessment 3 for the WLC group), and from reassessment following CBT-I to delayed reassessment (reassessment 1 to reassessment 3 for CBT-I group). The percentage of participants who meet the minimal clinically important difference (MCID) will also be reported (7 points for the ISI [36] and 3 points for the PSQI [39]). In the event that the data do not meet the assumptions for parametric *t* tests, nonparametric tests (Mann-Whitney *U* test for independent samples, and Wilcoxon signed rank test for paired samples) will be used.

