### Anticipated Limitations

Potential limitations related to the treatment response are as follows. First, it is unknown how each participant will respond to the CBT-I treatment with their current symptom burden. Enrolling participants who are within at least 4 weeks of their concussion was to obtain individuals who have relatively stable symptoms at the time of enrollment. Second, medication use and dosage may affect the treatment response to the CBT-I intervention. Therefore, information on medication will be collected at baseline and at reassessments to be included in statistical analysis if indicated. Third, participants will potentially be receiving care from other health care providers, which could impact the interpretation of the results. Therefore, information on type of services being received will be collected at baseline and at reassessments to be included in statistical analysis if indicated.

Another potential limitation to this study is attrition. The attrition rate was 20% in one study evaluating CBT-I in adolescents with a concussion [28]. A 20% attrition rate was also observed in a cognitive behavioral intervention study on adults who have had a concussion [58]. To account for attrition, we will overenroll by 20% in this study. To help with retention, study procedures and time commitment will be clearly articulated to potential participants and reinforced during the course of the study. Furthermore, individuals in the WLC will be contacted by telephone in the middle of their 6-week waiting period to remind them of their upcoming CBT-I sessions and to maintain connection and interest.

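### Aim 3 picks its covariates by testing baseline differences between the randomised arms, which does not identify the variables that could confound an association across participants

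*Protocol article*

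**What the plan says.** In the Protocol article, Statistical Approach, Aim 3 consists of two simple linear regressions. The first asks whether "change in ISI from preintervention to postintervention stages (predictor variable) will predict changes in postconcussion severity (dependent variable"). The second does the same for the number of symptoms. Neither has an arm term, and both arms receive CBT-I (Study Overview; WLC Activities).

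Covariates are governed by one rule. The trigger is "If there are significant differences at baseline in age, gender, medication use, number of concussions, and receiving other services between the two groups"; if it is met, "the variables will be entered into the model as a covariate, and the 2 models will be rerun". The simple regressions are therefore run first, and any adjusted models come second.

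A second, looser provision stands under Anticipated Limitations. There, "information on medication will be collected at baseline and at reassessments to be included in statistical analysis if indicated", and likewise "information on type of services being received will be collected at baseline and at reassessments to be included in statistical analysis if indicated". The article does not say what would count as an indication, nor which aim, model or time point is meant.

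The treatment effect itself is tested in Aims 1 and 2 by independent-samples t tests on percent change, with Mann-Whitney as the fallback. Neither test takes covariates. Under Randomization, the unblinded researcher who delivers the treatment "is also performing data analyses for this study".

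**The concern.** A test for baseline differences between arms addresses imbalance in an arm comparison, and Aim 3 is not one. It asks whether two changes go together across participants who all had CBT-I. A variable confounds that slope only if it is related to both changes. A service used equally in both arms that helped both sleep and symptoms would confound the slope fully and would not meet the trigger. A variable that differed between arms by chance but was unrelated to recovery would enter to no purpose.

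The candidate list is also closed at five variables. It omits arm and the preintervention PCSS score. Arm matters because the CBT-I window is weeks 0 to 6 in one group and weeks 6 to 12 in the other. Time since injury is absent too, although eligibility sets a minimum of 4 weeks and states no clear maximum.

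What is at stake is how the result is read. If the trigger fires, a rerun slope will be presented as adjusted. If it does not, the clean baseline table may be taken to mean that no adjustment was needed. Neither inference follows. Expected Findings and Conclusions lean on this association when they suggest that improving sleep may improve postconcussion symptoms.

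**Working it through.** The plan states no figure to reproduce here, so the check is on how the rule behaves.

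**Inputs.** Five candidate variables (Statistical Approach, Aim 3). Randomised groups of 20 and 20 (Randomization). A level of .05 for the baseline tests is an assumption: the article gives .05 only for the power analysis. Each variable is taken to be judged on its own test.

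**Step 1: how often the rule triggers.** Under randomisation every baseline difference is chance, so each variable passes its test with probability about .05, regardless of its relation to ISI or PCSS change.
- At least one of five, tests independent: 1 − 0.95^5 = 1 − 0.774 = 0.226, about 23%.
- Whatever the dependence between tests, the value lies between 5% (fully overlapping) and 5 × 0.05 = 25%.

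**Step 2: what that does to the slope.** Take one confounder with correlation r to both changes, independent of arm, and a true slope of 0 given the confounder. With standardised variables the unadjusted slope is r². The rule removes the bias only in the roughly 5% of trials where the variable happens to enter, so the expected slope is about 0.95 × r²:
- r = 0.3: unadjusted 0.09; rule 0.95 × 0.09 = 0.086
- r = 0.5: unadjusted 0.25; rule 0.95 × 0.25 = 0.238
- r = 0.7: unadjusted 0.49; rule 0.95 × 0.49 = 0.466

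A simulation of 40 participants, 10,000 runs per row, agrees. The values of r are assumptions, shown as a range.

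| r | Variable enters | Mean slope: unadjusted / rule / prespecified | Zero slope rejected at .05: unadjusted / rule / prespecified |
|---|---|---|---|
| 0.3 | 5.1% | 0.092 / 0.087 / 0.002 | 9% / 8% / 4.9% |
| 0.5 | 5.4% | 0.250 / 0.237 / 0.000 | 35% / 33% / 5.3% |
| 0.7 | 5.2% | 0.491 / 0.466 / 0.001 | 91% / 87% / 4.8% |

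Here the rule column takes the adjusted model when the trigger fires and the simple model otherwise. It is almost the same as no adjustment.

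**Step 3: the open clause on reassessment values.** This matters only for a model that estimates an arm effect. If a post-randomisation variable carries a share s of an effect of 0.8 (the planning value in Sample Size), adjusting for it leaves 0.8 × (1 − s): 0.72 for s = 10%, 0.60 for 25%, 0.40 for 50%. Simulation (4,000 runs each) gave 0.73, 0.60 and 0.40. With s = 0 the adjusted estimate was 0.81, so nothing was lost. The shares are assumptions.

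**The case against.** The strongest reply is that the stated Aim 3 hypothesis is one of association, and a simple regression answers it. That stands as far as it goes: the unadjusted models are always fitted and should be kept. But the protocol itself offers the rerun as the adjusted answer, and its criterion for entry is unsuited to that purpose.

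It can also be said that the simulated rejection rates rest on an assumed confounder and an assumed zero slope. They do, and they only illustrate the size of the problem. The entry rate of about 5% per variable does not depend on them.

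The Aim 3 rule is mechanical, so it leaves the analyst little discretion. That too stands. The combined role of therapist and analyst bears on the open clause in Anticipated Limitations, not on this rule.

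A reader might infer from that open clause that the plan adjusts away the treatment effect. The documents do not support this. Aim 3 has no arm term and so no treatment effect to lose. Aims 1 and 2 are specified as tests without covariates. The clause names no aim or model, and a fuller analysis plan may define it. Harm would require that the t tests be replaced by an adjusted model, that treatment change medication or services, and that these affect the outcome.

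Nor does the power of a baseline test to detect an imbalance add to the case. Between randomised arms there is no true difference to detect, and a difference between arms is not what matters for Aim 3.

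**Conclusion.** The point holds for the Aim 3 covariate rule. Followed as written, it selects on chance differences between arms and leaves confounding of the slope largely where it was: about 5% entry for any one variable and about 23% for at least one of five, assuming independent tests at .05. For an assumed confounder with r of 0.3 to 0.7, the rule moves the mean spurious slope only from 0.09 to 0.09, from 0.25 to 0.24, or from 0.49 to 0.47.

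The clause on reassessment medication and services is a secondary, conditional risk. It is an undefined option that could bias an arm comparison if it were used there.

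The primary ISI comparison is untouched by the Aim 3 rule, and Aim 3 is a non-primary aim of a study that calls itself a pilot. The change is worth making because it is cheap and because the article's conclusions draw on this association.

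**What to change.** - Delete the baseline-significance trigger.
- Keep the two unadjusted regressions. Add one prespecified adjusted version of each, fitted whatever the baseline table shows, with arm, the preintervention PCSS value (severity or count, to match the outcome) and receipt of other services.
- Define preintervention as the start of each arm's CBT-I window. For the waitlist group, which starts CBT-I 6 weeks after baseline, that is plausibly the week 6 reassessment and not baseline; the article should say which.
- Add time since injury if it was recorded at screening. It is not in the Demographics list, so this needs confirming.
- Put medication use and the remaining listed variables (age, gender, number of concussions) in a sensitivity model.
- In Anticipated Limitations, replace the open clause: any adjustment in Aims 1 and 2 uses baseline values only, and reassessment medication and services are reported descriptively or in a labelled sensitivity analysis.

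The cost is wording plus a few degrees of freedom. With services as one yes/no term, residual degrees of freedom fall from 40 − 2 = 38 to 40 − 5 = 35, or 34 with time since injury. With 32 participants they fall from 30 to 27, or 26. All variables other than time since injury are already being collected, and the article describes data collection as still open, so the models can be fixed before the final data are analysed.
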